#### **9.5.4. Exploratory endpoints**

Analyses of exploratory endpoints will be regarded as hypothesis-generating post-hoc analyses. Continuous endpoints will typically be analyzed by linear regression or median regression, as appropriate. Dichotomous endpoints will typically be analyzed by logistic regression.

#### **9.5.5. Safety Analysis**

Safety assessments and reporting of AEs and SAEs and other safety reporting are described in detail in [Section 8.3](#) and [Section 8.5](#), respectively. A Data Monitoring Committee will evaluate safety during the study ([Appendix 10.1.4](#)).

The safety set includes all randomized participants exposed to study intervention. General safety evaluations will be based on the occurrence, intensity, and type of AEs (including SAEs) in addition to causality. Safety analyses will be limited to tabulations of AEs/SAEs and subjects with AEs/SAEs.

### **9.6. Interim Analysis**

No interim analysis of efficacy is planned for this study

## **10. Supporting Documentation and Operational Considerations**

### **10.1. Appendix 1: Regulatory, Ethical, and Study Oversight Considerations**

#### **10.1.1. Regulatory and Ethical Considerations**

- This study will be conducted in accordance with the protocol and with the following:
  - Consensus ethical principles derived from international guidelines including the Declaration of Helsinki and Council for International Organizations of Medical Sciences (CIOMS) International Ethical Guidelines
  - Applicable ICH Good Clinical Practice (GCP) Guidelines
  - Applicable laws and regulations
- The protocol, protocol amendments, ICF, Investigator Brochure and other relevant documents (e.g., advertisements) must be submitted to an IRB/IEC by the investigator and reviewed and approved by the IRB/IEC before the study is initiated.
- Any amendments to the protocol will require IRB/IEC approval before implementation of changes made to the study design, except for changes necessary to eliminate an immediate hazard to study participants.
- Protocols and any substantial amendments to the protocol will require health authority approval prior to initiation except for changes necessary to eliminate an immediate hazard to study participants.
- The investigator will be responsible for the following:
  - Providing written summaries of the status of the study to the IRB/IEC annually or more frequently in accordance with the requirements, policies, and procedures established by the IRB/IEC
  - Notifying the IRB/IEC of SAEs or other significant safety findings as required by IRB/IEC procedures
  - Providing oversight of the conduct of the study at the site and adherence to requirements of 21 CFR, ICH guidelines, the IRB/IEC, European regulation 536/2014 for clinical studies (if applicable), European Medical Device Regulation 2017/745 for clinical device research (if applicable), and all other applicable local regulations

#### **10.1.2. Informed Consent Process**

- The investigator or his/her representative will explain the nature of the study to the participant or their legally authorized representative, and answer all questions regarding the study.

- Participants must be informed that their participation is voluntary. Participants will be required to sign a statement of informed consent that meets the requirements of local regulations, ICH guidelines, and the IRB/IEC or study center.
- The medical record must include a statement that written informed consent was obtained before the participant was enrolled in the study and the date the written consent was obtained. The authorized person obtaining the informed consent must also sign the ICF.
- Participants must be re-consented to the most current version of the ICF(s) during their participation in the study.
- A copy of the ICF(s) must be provided to the participant or their legally authorized representative.

Participants who are rescreened are required to sign a new ICF.

#### **10.1.3. Data Protection**

- Participants will be assigned a unique identifier by the sponsor. Any participant records or datasets that are transferred to the sponsor will contain the identifier only; participant names or any information which would make the participant identifiable will not be transferred.
- The participant must be informed that his/her personal study-related data will be used by the sponsor in accordance with local data protection law. The level of disclosure must also be explained to the participant who will be required to give consent for their data to be used as described in the informed consent
- The participant must be informed that his/her medical records may be examined by Clinical Quality Assurance auditors or other authorized personnel appointed by the sponsor, by appropriate IRB/IEC members, and by inspectors from regulatory authorities.

#### **10.1.4. Committees Structure**

##### **Data Monitoring Committee (DMC)**

A DMC will evaluate safety when 70 included patients have completed the 12 week follow-up, and again when these patients have completed the 52 week follow-up or are registered of study.

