**Brief Summary:**

The purpose of this study is to investigate whether palliative radiotherapy delivered 1-2 fractions of 8 Gy is non-inferior to palliative radiotherapy delivered in 5 fractions of 5 Gy with respect to change in patient-reported symptom intensity in patients with pelvic soft tissue tumors originating from either gastrointestinal, urological or gynecological cancer. Patients will define a target symptom as their main complaint according to study-specific predefined categories (pain, bleeding, bowel dysfunction, lower urinary tract dysfunction or vaginal dysfunction).

Patients will be randomly assigned to radiotherapy intervention with either 1-2 fractions of 8 Gy or 5 fractions of 5 Gy. Patients entering the study must be considered as candidates for palliative radiotherapy, and have a target symptom intensity at baseline of minimum 4 points on the NRS, which ranges from 0-10 with 0 indicating no symptom intensity and 10 indicating the worst symptom intensity imaginable.

For patients randomized to 1-2 fractions of 8 Gy, the second fraction will be offered if predefined criteria for unsatisfactory symptomatic response are met, assessed at the 4-week follow-up ([see Section 4.3.1](#)).

Assessment of endpoints will be performed at 4, 8, 12 (primary endpoint), 26 and 52 weeks after the radiotherapy is completed. Assessments include patient-reported evaluation of symptom intensity (NRS), QoL, overall patient satisfaction and physician-reported toxicities. Subjects will be followed with respect to overall survival until death, or censoring, defined as either loss to follow-up, study withdrawal or end of study.

The radiotherapy planning and deliverance, and the study-specific follow-up visits (attendance or by telephone) will be performed at the patients' local radiotherapy unit. Additional follow-up visits related to the patients' cancer disease will be performed at their local cancer department, and will be according to the institutional practice, independent of study inclusion.

Patients will be included over a period of 2-4 years with a maximum follow-up at study closure (overall survival).

The results of this study may contribute to the establishment of standard treatment recommendations, both nationally and internationally. Both interventions are currently being used in clinical practice, which will facilitate the implementation of study results.

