**Number of Participants:**

A maximum of 200 patients will be randomly assigned to study intervention to achieve a per protocol (PP) population of 146 patients

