### **9.3. Sample size determination**

The sample size determination was based on a one-sided two-sample *t* test. The sample size estimation is based on the following assumptions:

- One-sided T-test with 2,5 % significance level (equivalent to a two-sided 95 % CI)
- Standard deviation (SD) of the primary endpoint equal to 2
- Non-inferiority margin (NIM) of 1

With these assumptions, we will reach a power of 85 % if we enroll 146 patients. Based on the PallRad study, we assume an exclusion from intention to treat (ITT) - population of around 25 % (8, 9), and we will need to randomize a total number of 200 patients.

This number of patients also provide sufficient power to claim non-inferiority on the exploratory endpoints defined in [Section 9.1](#). The exclusion from ITT set is expected to be lower at 4 weeks, increasing the statistical power of conclusions.

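### The first DMC safety review counts only patients who complete week 12, so early deaths and drop-outs push it back (cheap improvement, minor)

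*Protocol*

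**What the plan says.** Protocol section 10.1.4 sets two DMC safety reviews in one sentence: "A DMC will evaluate safety when 70 included patients have completed the 12 week follow-up, and again when these patients" meet a second condition. The second trigger in full: "again when these patients have completed the 52 week follow-up or are registered of study", where the last words are evidently meant as off study. Section 9.6 plans no interim analysis of efficacy, and no other DMC date is given.

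Three other places bear on the timing. The Synopsis caps enrolment: "A maximum of 200 patients will be randomly assigned to study intervention". It also gives the accrual period: "Patients will be included over a period of 2-4 years". Section 9.3 gives the only loss rate: "we assume an exclusion from intention to treat (ITT) - population of around 25" per cent. Sections 9.4 and 9.5.5 define the safety set as every randomised participant exposed to radiotherapy, and section 9.5.5 refers to section 10.1.4 for the DMC's safety evaluation.

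**The concern.** The two triggers treat losses differently within one sentence. The second can be met by leaving the study; the first can be met only by completing week 12. The more patients are lost early, the longer the first review waits, which is the wrong direction for a safety trigger. The second review is tied to the same 70 patients and inherits the delay.

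Early loss is to be expected here. Section 5.1 admits ECOG 0-3, section 2 says that clinicians tend to overestimate survival, and sections 2.2.2.2 and 2.2.2.3 cite median survival of 9 months (rectal) and 20 months (prostate) in the earlier Norwegian study. What is at stake is the number of further patients randomised before the DMC first meets.

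**Working it through.** **The plan's own figures.** Section 10.1.4 gives no derived figure. The loss rate comes from section 9.3, so that calculation was checked first. With one-sided alpha 0.025, SD 2, margin 1 and true difference 0, the exact t-test power at 73 per arm (146 in total) is 0.851, against 85% stated. Then 146/0.75 = 194.7, or 195, against 200 stated. Both agree with the plan.

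**Inputs.** Trigger of 70 (10.1.4); 200 randomised over 2-4 years (Synopsis); share d missing week 12. The protocol does not state d. I use 25% (borrowed from 9.3), 15% and 0%. Further assumptions: even accrual, patients reach week 12 in order of randomisation, and no lag from randomisation to the end of radiotherapy.

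**Formulas.** Weekly accrual r = 200/(52 × years) = 1.92, 1.28 and 0.96 for 2, 3 and 4 years.

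- Randomised patients needed for 70 completers: 70/(1 − d) = 93.3 (25%), 82.4 (15%), 70 (0%).
- Randomised at review 1: 70/(1 − d) + 12r.
- Randomised at review 2: 70/(1 − d) + 52r.

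| Share missing week 12 | Review 1 (2 / 3 / 4 years) | Review 2 (2 / 3 / 4 years) |
|---|---|---|
| 25% | 116 / 109 / 105 | 193 / 160 / 143 |
| 15% | 105 / 98 / 94 | 182 / 149 / 132 |
| 0%, or off-study patients counted | 93 / 85 / 82 | 170 / 137 / 120 |

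**Delay due to the missing clause.** This is 70/(1 − d) − 70 patients: 93.3 − 70 = 23.3 at 25%, 82.4 − 70 = 12.4 at 15%, and 0 at 0%. While accrual continues, it does not depend on the accrual rate. In calendar time, 23.3/r is about 12, 18 and 24 weeks for 2, 3 and 4 years of accrual; 12.4/r is about 6, 10 and 13 weeks.

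**Sensitivity.** A two-week lag to the end of radiotherapy adds 2r, about 2-4 patients, to every entry and leaves the differences unchanged. With a 26-week linear ramp-up, review 1 falls at 120, 110 and 106 (25%) against 96, 87 and 82 (0%), a difference of 23-24.

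**Is a loss of this order plausible?** Twelve weeks is 2.77 months. Under exponential survival, deaths before week 12 would be 1 − 0.5^(2.77/9) = 19% with a 9-month median and 1 − 0.5^(2.77/20) = 9% with a 20-month median. These count deaths only and are illustrative.

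**The case against.** The strongest reply is that section 10.1.4 fixes when the DMC meets and not whose data it sees. A reader might infer that early deaths and drop-outs are hidden from the DMC. The documents do not support that: the safety set is all exposed patients, and nothing limits a review to the 70. This part of the reply stands.

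Nor does early harm wait for the meeting. SAEs go to the sponsor within 24 hours (8.5.1), all grade 3 or higher events are collected through week 4, and the study can be stopped at any time. This mostly stands. However, deaths clearly due to progression are not recorded as SAEs (10.3.2), and after week 4 (week 8 after a second fraction) only events with probable or definite causality are reported. The scheduled review therefore still has a role.

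A reader might also think that excess loss in one arm adds delay of its own. It does not: the trigger pools both arms, so only total loss matters.

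The 25% is borrowed. It is an assumed exclusion from the analysis population, and the per-protocol sets in section 9.4 also drop ineligible patients and major deviations. The week-12 loss may be lower, so the range must be shown.

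Finally, counting completers guarantees 70 full 12-week assessments at the first review. That is a legitimate aim, and the fix gives some of it up.

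**Conclusion.** The point holds as a minor defect of timing. The first trigger lacks the off-study clause that the second has, so early losses delay the first review and, through the shared cohort, the second. The delay is about 23 randomised patients at 25% loss, about 12 at 15% and none at 0%. This assumes even accrual of 200 over 2-4 years and completion in order of randomisation.

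It would be tempting to go further and say that the trigger wording makes the 52-week review too late, so that another review is required. The figures do not support this. With the clause added, review 2 still falls at 120-170 randomised (60-85% of 200). Its lateness comes mainly from a year of follow-up set against 2-4 years of accrual. An extra look after accrual could not change radiotherapy already given, and week-52 toxicity is already in the planned analyses (9.4, 9.5.3). A DMC charter may add detail, but it is not at hand.

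**What to change.** In section 10.1.4, add to the first trigger the clause that the second already has, for example: *when 70 treated patients have completed the 12-week follow-up or are registered off study*. Keep the second trigger, correcting its spelling of off study. As a clarification, say that each review covers the safety set; this can stand here or in the charter. No further review needs to be added.

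The cost is one line of wording. The downside is fewer completed 12-week visits at the first review: about 70 × 0.75 = 52.5 at 25% loss or 70 × 0.85 = 59.5 at 15%, instead of 70. Dose, endpoints and sample size are unaffected.

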##### **Steering Committee**

Will oversee the general conduct of the study

#### **10.1.5. Data Quality Assurance**

- All participant data relating to the study will be recorded on printed or electronic CRF unless transmitted to the sponsor or designee electronically (e.g., laboratory data). The

investigator is responsible for verifying that data entries are accurate and correct by physically or electronically signing the CRF.

- The investigators must maintain accurate documentation (source data) that supports the information entered in the eCRF.
- Study monitors will perform ongoing source data verification to confirm that data entered into the eCRF by authorized site personnel are accurate, complete and verifiable from source documents; that the safety and rights of participants are being protected; and that the study is being conducted in accordance with the currently approved protocol and any other study agreements, ICH GCP, and all applicable regulatory requirements.
- The investigator must permit study-related monitoring, audits, IRB/IEC review, and regulatory agency inspections and provide direct access to source data documents.
- Monitoring details describing strategy (e.g., risk-based initiatives in operations and quality such as Risk Management and Mitigation Strategies and Analytical Risk-Based Monitoring), methods, responsibilities and requirements, including handling of noncompliance issues and monitoring techniques (central, remote, or on-site monitoring) are provided in the Monitoring Plan.
- The sponsor or designee is responsible for the data management of this study including quality checking of the data.
- The sponsor assumes accountability for actions delegated to other individuals (e.g., Contract Research Organizations).
- Records and documents, including signed ICFs, pertaining to the conduct of this study must be retained by the investigator for 15 years after study completion unless local regulations or institutional policies require a longer retention period. No records may be destroyed during the retention period without the written approval of the sponsor. No records may be transferred to another location or party without written notification to the sponsor.

#### **10.1.6. Source Documents**

- Source documents provide evidence for the existence of the participant and substantiate the integrity of the data collected. Source documents are filed at the investigator's site.
- Data reported on the CRF or entered in the eCRF that are transcribed from source documents must be consistent with the source documents or the discrepancies must be explained. The investigator may need to request previous medical records or transfer records, depending on the study. Also, current medical records must be available.
- Definition of what constitutes source data can be found in the Investigator Site File.

- The investigator must maintain accurate documentation (source data) that supports the information entered in the CRF.
- Study monitors will perform ongoing source data verification to confirm that data entered into the CRF by authorized site personnel are accurate, complete, and verifiable from source documents; that the safety and rights of participants are being protected; and that the study is being conducted in accordance with the currently approved protocol and any other study agreements, ICH GCP, and all applicable regulatory requirements.

#### **10.1.7. Study and Site Start and Closure**

##### **First Act of Recruitment**

The study start date is the date on which the clinical study will be open for recruitment of participants.

The first act of recruitment is the first site open and will be the study start date.

##### **Study/Site Termination**

The sponsor or designee reserves the right to close the study site or terminate the study at any time for any reason at the sole discretion of the sponsor. Study sites will be closed upon study completion. A study site is considered closed when all required documents and study supplies have been collected and a study-site closure visit has been performed.

The investigator may initiate study-site closure at any time, provided there is reasonable cause and sufficient notice is given in advance of the intended termination.

Reasons for the early closure of a study site by the sponsor or investigator may include but are not limited to:

For study termination:

- Discontinuation of further study intervention development

For site termination:

- Failure of the investigator to comply with the protocol, the requirements of the IRB/IEC or local health authorities, the sponsor's procedures, or GCP guidelines
- Inadequate or no recruitment (evaluated after a reasonable amount of time) of participants by the investigator
- Total number of participants included earlier than expected

If the study is prematurely terminated or suspended, the sponsor shall promptly inform the investigators, the IECs/IRBs, the regulatory authorities, and any contract research organization(s) used in the study of the reason for termination or suspension, as specified by the applicable

regulatory requirements. The investigator shall promptly inform the participant and should assure appropriate participant therapy and/or follow-up

#### **10.1.8. Publication Policy**

- The results of this study will be published in international, peer review journals and will be presented at scientific meetings. If this is foreseen, the investigator agrees to submit all manuscripts or abstracts to the sponsor before submission. This allows the sponsor to protect proprietary information and to provide comments.
- The sponsor will comply with the requirements for publication of study results. In accordance with standard editorial and ethical practice, the sponsor will generally support publication of multicenter studies only in their entirety and not as individual site data. In this case, a coordinating investigator will be designated by mutual agreement.
- Authorship will be determined by mutual agreement and in line with International Committee of Medical Journal Editors authorship requirements.

## **10.2. Appendix 2: Clinical Laboratory Tests**

See [section 8.3.3](#) and [8.3.5](#).

### 10.3. Appendix 3: AEs and SAEs: Definitions and Procedures for Recording, Evaluating, Follow-up, and Reporting

#### 10.3.1. Definition of AE

| AE Definition                                                                                                                                                                                                                                                                                                                                                                                                                                                                   |
|---------------------------------------------------------------------------------------------------------------------------------------------------------------------------------------------------------------------------------------------------------------------------------------------------------------------------------------------------------------------------------------------------------------------------------------------------------------------------------|
| 
 
• An AE is any untoward medical occurrence in a clinical study participant, temporally associated with the use of study intervention, whether or not considered related to the study intervention.
 
• NOTE: An AE can therefore be any unfavorable and unintended sign (including an abnormal laboratory finding), symptom, or disease (new or exacerbated) temporally associated with the use of study intervention.
 
 |

| Events Meeting the AE Definition                                                                                                                                                                                                                                                                                                                                                                                                                                                                                                                                                                                                                                                                                                                                                                                                                                                                                                                                                                                                                                                                                                                                                                                                                                                                                                                                                                                                                                                      |
|---------------------------------------------------------------------------------------------------------------------------------------------------------------------------------------------------------------------------------------------------------------------------------------------------------------------------------------------------------------------------------------------------------------------------------------------------------------------------------------------------------------------------------------------------------------------------------------------------------------------------------------------------------------------------------------------------------------------------------------------------------------------------------------------------------------------------------------------------------------------------------------------------------------------------------------------------------------------------------------------------------------------------------------------------------------------------------------------------------------------------------------------------------------------------------------------------------------------------------------------------------------------------------------------------------------------------------------------------------------------------------------------------------------------------------------------------------------------------------------|
| 
 
• Any abnormal laboratory test results (haematology, clinical chemistry, or urinalysis) or other safety assessments (e.g., ECG, radiological scans, vital signs measurements), including those that worsen from baseline, considered clinically significant in the medical and scientific judgment of the investigator (i.e., not related to progression of underlying disease).
 
• Exacerbation of a chronic or intermittent pre-existing condition including either an increase in frequency and/or intensity of the condition.
 
• New conditions detected or diagnosed after study intervention administration even though it may have been present before the start of the study.
 
• Signs, symptoms, or the clinical sequelae of a suspected intervention- intervention interaction.
 
• Signs, symptoms, or the clinical sequelae of a suspected overdose of either study intervention or a concomitant medication. Overdose per se will not be reported as an AE/SAE unless it is an intentional overdose taken with possible suicidal/self-harming intent. Such overdoses should be reported regardless of sequelae.
 
• The signs, symptoms, and/or clinical sequelae resulting from lack of efficacy will be reported as AE or SAE if they fulfil the definition of an AE or SAE. “Lack of efficacy” or “failure of expected pharmacological action” also constitutes an AE or SAE.
 
 |

| Events NOT Meeting the AE Definition |
|---------------------------------------------|
|---------------------------------------------|

- Any clinically significant abnormal laboratory findings or other abnormal safety assessments which are associated with the underlying disease, unless judged by the investigator to be more severe than expected for the participant's condition.
- The disease/disorder being studied or expected progression, signs, or symptoms of the disease/disorder being studied, unless more severe than expected for the participant's condition.
- Medical or surgical procedure (e.g., endoscopy, appendectomy): the condition that leads to the procedure is the AE.
- Situations in which an untoward medical occurrence did not occur (social and/or convenience admission to a hospital).
- Anticipated day-to-day fluctuations of pre-existing disease(s) or condition(s) present or detected at the start of the study that do not worsen.

